### The intervention: *Connect Local*

3.4

The *Connect Local* program will involve eligible individuals to access a trained and paid Community Connecter professional. Community Connectors are individuals with a counselling, community development, health/allied health professional and/or life coaching background, who receive training in social prescribing (55), wellness and reablement and positive ageing, diversity in ageing, mental health first aid and trauma informed care.

Once a referral/contact is received, the *Connect Local* program manager contacts the community member and first discusses the program, to ascertain that it is what they are seeking. If so, the community member is screened for eligibility, namely, they live in target geographic location, are aged 65 or older, have a chronic health condition, and are in need of social connection. If appropriate, the program manager organises the Community Connector to contact the individual to organise a time to meet face to face and commence the program. As shown in Figure 3, the Community Connector will work with eligible community members to:

**Identify** what matters to the individual and screen for loneliness, social isolation and depressive symptoms: the Community Connector holds a rapport-building conversation, involving open-ended questions and using motivational interviewing techniques guided by the NHS document ‘What matters to me?’ (56). The question topics have previously been codesigned with Community Connectors and community members to ensure they are fit-for-purpose for the local population, and include: expectations of the program, personal history in the area, past activities of interest, and when they remember being happy – where they were, who they were with, and what they were doing;**Work together** on generating goals that address a social need/s, and a develop a **plan** to achieve these goals by linking the individual to activities and/or services being offered in the target geographic area. This is based on the discussion on “What matters to me?” and what existing available programs and activities are in the region, as well as the community member’s level of digital engagement and any transportation requirements. Usually three or four programs/activities are generated for pursuing;**Support** the individual to access these activities/services using local resources such as volunteer support including transport. This involves the Community Connector reaching out to program/activity providers agreed to in point 2, and organising to meet with the community member at the program/activity location. This serves as an introduction and, if possible, have the community member participate or at least view the program/activity, to ascertain whether this is something they are interested in engaging with. If the community member is interested, the Community Connector facilitates ongoing engagement in the program/activity, as needed. If the community member is not interested in this program/activity, they pursue an alternative program/activity discussed previously; and.**Review** follow up to ensure that the activities and/or services are addressing their needs. Should there be any issues, the Community Connector may either engage with the service/activity provider to address them or work with the individual to develop a new goal, plan and access new activity/service.

**Figure 3 fig3:**
[figure not shown]
Service flow of *Connect Local*. Adapted from Mann et al. (20).

Individuals who participate in all four elements will be considered to have completed the full program. Meetings between the Community Connector and the participant will be undertaken in a mutually agreed upon location, including local community houses, local spaces such as libraries, local cafés, or in the participant’s home.

People will be engaged in the program through multiple sources: the local tertiary hospital, aged care provider, general practices, allied health providers, community health providers, through the program website, and general community access.

#### Comparator group (usual care)

3.4.1

These individuals will receive usual care (regular access to activities in their LGA), and will not be engaged in the *Connect Local* program.

### Participants of the evaluation

3.5

There are three participant groups involved in this evaluation: older community members, community volunteers, and health and social care providers.

#### Older community members: intervention group

3.5.1

The inclusion criteria include being aged 65 years or older; understand and speak English sufficiently to understand and be involved in the program; live in the target LGA; community dwelling (including those experiencing homelessness); have at least one chronic health condition; are at risk or experiencing loneliness, social isolation and/or depressive symptoms. Screening tools are summarised in Table 2, loneliness will be assessed using both the Single Item Measure and UCLA-3 as per recommended national indicators of loneliness (66).

**Table 2 tab2:** Intervention outcome evaluation methods.

Evaluation component *Definition*	Indicators	Methods and tools
Individual level *Impacting individuals directly*	*Older person participants:*	
	Loneliness	Single-item measure of loneliness: How often do you feel lonely?, responses: often or always, some of the time, occasionally, hardly ever or never (often or always, some of the time indicating loneliness)	UCLA-4 (57)
UCLA-3 (score of ≥6 indicates at risk of loneliness) (58)
Social isolation	Lubben-6 (score ≤ 12 indicates at risk for social isolation) and − 18 (59);
Social anxiety	Mini-SPIN (Social Phobia Inventory, SPIN) (60);
Depressive symptoms	GDS-5 (score of ≥2 is indicative of depression) (61);
Wellbeing and quality of life	Physical wellbeing (and QoL): EQ-5D-5L (62); Mental wellbeing: Warwick-Edinburgh Mental Wellbeing Scale (WEMWBS) (63);
Goals attained^+^	Goal Attainment (64)^+^.
Perceptions of program^+^	Interviews on perceptions of the program^+^.
*Service providers:*	
Perceptions of program	Interviews/focus groups on perceptions of the program.
*Volunteers:*	
Wellbeing and quality of life	Physical wellbeing (and QoL): EQ-5D-5L (62); Mental wellbeing: Warwick-Edinburgh Mental Wellbeing Scale (WEMWBS) (63);
Perceptions of program	Interviews/focus groups onperceptions of the program.
Community level *Impacting broader community*	*Older person participants:*	
	Access to activities/services Number and types of services offered to participants	Resource use questionnaire [adapted from Fletcher et al. (65)]
	*Community service providers:*	
	Impact of program on community services	Community service impact survey [adapted from NHS (56)]
	Community service provider Satisfaction with program	Interview/focus group with community service providers
Health system level *Impacting at the health service level, including hospitalisations, GP visits and other health service visits.*	*Older person participants:*	
	ED presentations; Hospitalisations; Hospital length of stay Number of GP consultations Number of GP care plan reviews	Resource use questionnaire [adapted from Fletcher et al. (65)]
	*Health Service providers:*	
	Perspectives of staff in general practice and other referral agencies Health provider satisfaction	Interviews/focus groups

^+^Data not being collected from community members in comparator group.

The exclusion criteria include living in residential aged care; individuals who do not speak English sufficiently to understand the program; and individuals who do not have the cognitive capacity to consent [assessed using a Cognitive Capacity to Consent Checklist (67)].

All eligible individuals will be made aware of the evaluation by the Community Connector and asked if their details can be shared with the researchers to contact them about the study. The researchers will contact the individuals to obtain consent. If consent is obtained, individuals will be asked if they would like to be informed of trial results.

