**Methods:**

A Type 1 Hybrid design, including program effectiveness, cost-effectiveness, and implementation evaluation of the *Connect Local* program, will be undertaken. Eighty-eight participants aged ≥65 years with one or more chronic health condition, who are also either experiencing or at risk of loneliness, social isolation and depressive symptoms will be invited to participate in the evaluation. Outcomes, measured at baseline, 3, 6 and 12 months, include loneliness, social isolation, depressive symptoms, social anxiety, goal attainment, wellbeing, quality of life and health care utilisation. A gender and age matched comparator group of 88 individuals will be recruited from outside the intervention local government area. Impact of the intervention on community service providers in the target region will be evaluated using mixed methods, where triangulation will be used to combine the qualitative and quantitative data using a deductive-simultaneous design. Changes in wellbeing and quality of life of community volunteers will also be measured. All groups will be interviewed to ascertain their experience and perceptions of the program. The economic evaluation will use a Social Return on Investment (SROI) approach, to include outcomes at the individual, community, and system levels. Implementation outcomes will consider Reach, Adoption, Feasibility, Acceptability, Appropriateness, Fidelity, and Sustainability of the intervention.

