#### Older community members: comparator

3.5.2

Given the proposed whole of community impact of *Connect Local* program, the inclusion criteria for the comparator group are the same as for the intervention group, except that they do not live in the target LGA. These participants will be recruited from the local tertiary hospital and aged and community care provider. All eligible individuals will be made aware of the program through their care provider and will be asked if their details can be shared with the researchers to contact them about the study. The researchers will contact the individuals to obtain consent. Recruitment will be monitored in blocks of five to match comparator participants by age and gender to the intervention participant group.

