##### Individual level

3.6.2.1

This is the level at which individuals are impacted directly, including older community members, volunteers and health and social service providers.

For older community members, we will consider the primary outcome as a mean change in loneliness, from baseline at 3, 6 and 12 months for participants receiving the *Connect Local* program, when compared to the comparator group. This will be measured using UCLA-3 as informed by previous research that support the sample size calculations (58). At this stage, there is insufficient research data to calculate sample size when using UCLA-4 (57), however this tool has been recommended for use by community organisations by Australia’s national network, Ending Loneliness Together (71), therefore we will also utilise this tool to capture loneliness to ascertain whether it can be utilised with this cohort in future studies.

As outlined in Tables 2, 3, secondary outcomes, including social isolation, social anxiety, depressive symptoms, and improvement in quality of life and wellbeing, are a mean change from baseline at 3, 6 and 12 months for participants receiving the *Connect Local* program, when compared to the comparator. Achieved goals, as measured by the Goal Attainment scale (64), will also be gathered from the intervention group.

For community volunteers involved in the *Connect Local* program, as per Tables 2, 3, we will collect health-related quality of life and wellbeing measures at baseline, 3, 6 and 12 months.

Perceptions of the program will be collected from community members in the intervention group, volunteers and service providers involved in referred to the *Connect Local* program through interviews or focus groups at three months from participant baseline. Questions will invite participants to share their thoughts around the following aspects of the program: Relational (trust and trustworthiness, obligations and expectations, identity and identification), Cognitive (shared language, codes and narratives; shared values, attitudes and beliefs; and shared goals and purpose), and Structural (roles, rules, precedents and procedures).

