For quantitative, binary or dichotomous individual level outcomes (scales that have cut-off scores: loneliness (UCLA-3), social anxiety, depressive symptoms) additional analysis will be undertaken addressing the research question: do the interventions differ in their effectiveness, such that individuals in the intervention group experience a greater improvement in their probability of achieving the desired outcome compared to those receiving usual care. Generalised linear mixed models (GLMMs) for dichotomous outcomes will be used as well as GEE. The typology of missing data will be investigated to make sure that the assumptions of the adopted statistical technique are not violated. Our choice of GLMMs is based on the specific characteristics of the data, as well as the advantages provided by GLMMs in handling dependent responses in longitudinal or repeated measures studies. As highlighted in Breslow and Clayton (75), GLMMs incorporate random effects into the linear predictors and are particularly well-suited for modelling the dependence among response variables in such study designs.

Selection of the model that best fits the data will be based on the low goodness-of-fit measures such as the Akaike information criterion (AIC) and Bayesian information criterion (BIC). Additionally, the log-likelihood ratio test will be employed as another method for evaluating model fit.

All quantitative community and system level variables, as well as the goal attainment will be analysed descriptively. Descriptive statistics will be presented as proportions, means (standard deviations) or, for variables that did not conform to a normal or log-normal distribution, medians (interquartile range).

Statistical analysis will be performed using STATA V.15.0 (STATA Corp LP., College Station, Texas, United States). We will use a Type I error rate of 5% to indicate statistical significance, with 95% confidence intervals (CI).

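### Loneliness status at entry is neither required nor matched, so the two non-randomised groups can differ in it and drift apart on UCLA-3 without any program effect

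*Protocol article*

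**What the plan says.** **Entry.** Section 3.5.1 of the protocol article accepts older people who "are at risk or experiencing loneliness, social isolation and/or depressive symptoms". Table 2 gives each problem its own cut-off: UCLA-3 of 6 or more for loneliness, Lubben-6 of 12 or less for isolation, GDS-5 of 2 or more for depressive symptoms. A positive loneliness screen is not a condition of entry. For the comparator, section 3.5.2 states that "the inclusion criteria for the comparator group are the same as for the intervention group, except that they do not live in the target LGA".

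**Primary outcome.** Section 3.6.2.1 states: "we will consider the primary outcome as a mean change in loneliness, from baseline at 3, 6 and 12 months", measured by UCLA-3 and compared with the comparator group.

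**Group formation.** Section 3.3 describes a non-randomised convenience sample. Under section 3.4, intervention participants come through the hospital, the aged care provider, general practices, allied and community health, the website and general community access. Under section 3.5.2, comparators come from the hospital and the aged and community care provider only. On matching, that section says: "Recruitment will be monitored in blocks of five to match comparator participants by age and gender to the intervention participant group".

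**Model.** Section 3.7.1.1 gives the mean structure as group, time and their interaction.

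**The concern.** The Introduction itself separates loneliness from social isolation, yet either one opens the door to a study whose primary endpoint is loneliness. Each group will therefore probably mix people above and below the UCLA-3 cut-off, and nothing in the recruitment rules makes the two mixtures alike.

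People who score high when enrolled tend to score lower later without any intervention. People who score low have less room to fall and may rise. If one group holds more of the first kind, the groups will change by different amounts under usual care alone. The primary analysis reads exactly that quantity, the difference in change, as the program effect. If the intervention group is the lonelier one, the error favours the program. If the comparator is lonelier, it hides a benefit.

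The routes into the two groups make such a difference plausible. Under section 3.4, intervention participants are first asked whether the program is what they want and are screened as needing social connection. Comparators are approached through their care provider.

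**Working it through.** **1. The target used as a yardstick.** Section 3.6.2.3.1 gives a 0.85-point fall in UCLA-3 and an effect size of 0.37, so the implied SD is 0.85 / 0.37 = 2.30. The stated sample size reproduces, to rounding, as a two-sided, one-sample calculation: ((1.960 + 1.282) / 0.37)² = 76.75, against a stated 76. Then 76 × 1.15 = 87.4, rounded up to the stated 88. The calculation applies 0.37 to every participant, whatever their loneliness at entry.

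**2. Can a non-lonely person enter?** Yes. Someone with Lubben-6 of 12 and UCLA-3 below 6 meets the rule in either group. The article does not say how many such people to expect.

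**3. Bias from unequal shares.** Let p_I and p_C be the shares lonely at entry in the intervention and comparator groups, and m the average natural fall among lonely people. Assume non-lonely people do not change. With no program effect:

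- change in the intervention group = −p_I × m
- change in the comparator group = −p_C × m
- spurious difference in change = −(p_I − p_C) × m

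For shares of 80% and 60% and m = 0.5, the absolute difference is 0.20 × 0.5 = 0.10 points. That is 0.10 / 0.85 = 12% of the target, or 0.10 / 2.30 = 0.04 SD. The shares and m are assumptions, so a range is needed:

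| Natural fall m (points) | Gap of 10 points in share | Gap of 20 points | Gap of 30 points |
|---|---|---|---|
| 0.3 | 0.03 (3.5% of 0.85) | 0.06 (7.1%) | 0.09 (10.6%) |
| 0.5 | 0.05 (5.9%) | 0.10 (11.8%) | 0.15 (17.6%) |
| 0.85 | 0.085 (10.0%) | 0.17 (20.0%) | 0.255 (30.0%) |

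If non-lonely people also drift upward by u points, m is replaced by m + u and each figure grows.

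**4. Does the stated model remove this?** Baseline is one of the measured time points, so a constant difference in level between groups cancels in the change. A difference in the rate of natural change does not cancel: it falls entirely in the group-by-time term.

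**5. Dilution, as a bound only.** Suppose a share f of entrants is not lonely and gains nothing. The mean effect is then 0.37 × (1 − f), and power on the article's own one-sample basis with n = 76 is Φ(0.37 × (1 − f) × √76 − 1.96):

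| f (assumed) | Effect | Power if non-lonely gain nothing | Power if they gain half the effect |
|---|---|---|---|
| 0 | 0.370 | 0.90 | 0.90 |
| 20% | 0.296 | 0.73 | 0.83 |
| 30% | 0.259 | 0.62 | 0.78 |

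The effect column applies to the no-gain case. These figures show sensitivity and do not estimate what will happen. Neither f nor the gain among non-lonely entrants is in the article.

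**The case against.** **Dilution may be slight or already counted.** The 0.85 comes from a program described only as similar. If that program also took a mixed group, the figure already includes non-lonely people, and multiplying by (1 − f) would dilute it twice. UCLA-3 of 6 is an at-risk mark and is not presented as the bottom of the scale, so people below it may still fall. The endpoint is a difference between groups, so preventing a rise is also a benefit, and the Discussion presents the program as early and preventative. All of this stands. A reader might infer that the trial enrols people in whom the outcome cannot occur and is underpowered for that reason. The article does not support that.

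**The cut-off analysis is not invalid.** A reader might infer that entrants below 6 at baseline are counted as successes. Section 3.7.1.1 asks about "greater improvement in their probability of achieving the desired outcome compared to those receiving usual care", using repeated-measures models, so it concerns change between groups over time. Such entrants can lower its sensitivity, but they do not make it wrong.

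**Restricting the primary population would change the question.** The trial is pragmatic, and its research question covers the people the program serves. A lonely-only primary set is a different estimand, and selecting on the outcome scale brings more regression to the mean.

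**The imbalance illustration is small and rests on invented inputs.** It is, and the inputs are labelled as assumptions. Both groups also share the same entry rule, and adjustment for baseline characteristics may be set out in an analysis plan that is not shown, so its absence here is no fault. None of this removes the point about matching. That is a recruitment decision fixed in this article, the sources differ, and the one characteristic most closely tied to the primary outcome is left uncontrolled.

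**The abstract.** Its wording, "who are also either experiencing or at risk of loneliness, social isolation and depressive symptoms", joins the three problems with *and*, where section 3.5.1 has *and/or*. This is loose phrasing; other sections agree with 3.5.1.

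**Conclusion.** The point holds as a weakness in how the comparator is formed. Entry is open to any of three problems, the primary outcome concerns one of them, and matching ignores it, so the groups may differ in natural change on UCLA-3. On the assumptions tabulated, the resulting error runs from 0.03 to 0.255 points (3.5% to 30% of the 0.85 target), with 0.10 points in the middle case. Its direction cannot be known in advance. Whether a gap in the lonely share will arise at all is not shown by the article, only that nothing in the recruitment rules prevents it.

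Dilution is possible but cannot be quantified from the article, and zero effect in non-lonely entrants is the worst case. It does not justify changing who counts for the primary outcome. Overall this is a cheap improvement worth making and does not invalidate the design.

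**What to change.** **Change.** In section 3.5.2, add loneliness-screen status (UCLA-3 of 6 or more versus below 6) to age and gender as a matching factor, using the existing monitoring in blocks of five. Table 3 already schedules UCLA-3 at screening, so no new data are needed. Report the share at or above 6 in each group.

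**Optional addition.** Repeat the mean-change and cut-off analyses among participants with UCLA-3 of 6 or more at baseline. Label these as supportive and leave the primary population as it is.

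**Editorial.** Bring the abstract's eligibility wording into line with section 3.5.1.

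**Cost.** A third yes/no factor makes comparator recruitment slightly slower. Program access is unaffected. A two-level match reduces the imbalance without removing it: the groups may still differ in UCLA-3 within each level, and in characteristics nobody has matched.

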#### Procedures

3.6.1

Data will be collected either by researchers via the phone, in-person, in paper-based surveys, or by Community Connectors during program operations. Study data will be collected and managed using REDCap electronic data capture tools hosted on a secure server at Bolton Clarke (68), which only researchers will have access by password. Table 2 outlines the different levels and the data collected, while Table 3 outlines the time points of data collection. If data collection causes distress to participants, interviewing will be immediately halted and existing escalation procedures will be followed, including referral back to the referring healthcare provider (community members), service responsible (volunteers), or external mental health services.

**Table 3 tab3:** Schedule of enrolment, interventions and assessments, per SPIRIT guidelines (50).

	Study period				
Timepoint:	Screening	Baseline	3-months	6-months	12-months
Enrolment					
Screening	X				
Informed consent	X				
Intervention					
*Connect Local* intervention					
Usual care (no intervention)					
Assessments					
Single-item measure of loneliness (69)	X				
UCLA – LS 3 (58).	X	X	X	X	X
Lubben Social Network Scale (LSNS-6) (70).	X				
5 item Geriatric Depression Scale (GDS 5) (61).	X	X	X	X	X
Demographic information		X			
UCLA-LS4 (71).		X	X	X	X
Lubben Social Network Scale (LSNS-18) (59)		X	X	X	X
Mini-Social Phobia Inventory (Mini-SPIN) (60).		X	X	X	X
Warwick-Edinburgh Mental Wellbeing Scale (WEMWBS) (63);		X	X	X	X
EQ-5D-5L (62);		X	X	X	X
Goal attainment (64).		X	X	X	X
Community service impact survey				X	X
Resource use questionnaire		X	X	X	X
Perceptions (acceptability), use and satisfaction with program			X		
Process data			X	X	X
Perspectives of staff in General practice and other referral agencies			X	X	X

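### The described recruitment route allows intervention-group baseline UCLA-3 to be taken after the first Community Connector session, and nothing visible in the article requires it to come earlier

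*Protocol article*

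**What the plan says.** Section 3.4 describes entry to the program. The program manager makes the first contact, at which "the community member is screened for eligibility, namely, they live in target geographic location, are aged 65 or older, have a chronic health condition" and a need for social connection; no instrument is named. If the person is suitable, the manager "organises the Community Connector to contact the individual to organise a time to meet face to face and commence the program".

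The first of the four program elements is to identify "what matters to the individual and screen for loneliness, social isolation and depressive symptoms: the Community Connector holds a rapport-building conversation". The text under Figure 3 confirms that this element is part of the intervention: "Individuals who participate in all four elements will be considered to have completed the full program". Goals are generated in the second element.

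Section 3.5.1 makes being at risk of, or experiencing, loneliness, isolation and/or depressive symptoms an inclusion criterion for the evaluation, using the Table 2 tools. The invitation route is then given: "All eligible individuals will be made aware of the evaluation by the Community Connector", after which "The researchers will contact the individuals to obtain consent".

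Table 3 (section 3.6.1) has a Screening column containing the screen and informed consent, followed by a Baseline column. UCLA-3 and GDS-5 appear in both. Goal attainment is listed at Baseline.

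Section 3.5.2 recruits comparators through their care provider, without Connector contact. Section 3.6.2.1 defines the primary outcome as mean change in UCLA-3 from baseline against the comparator group. Section 3.2 bases the economic case partly on comparing the situation before the intervention with the situation after it.

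**The concern.** A change-from-baseline outcome needs a baseline that precedes exposure. Here the person who invites people to the evaluation also delivers the intervention, and the score-based screen sits inside the first element of that intervention. If the sequence is followed in the order described, the intervention group's baseline is taken after a rapport-building, motivational conversation, and the comparator group's is not.

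Two consequences would follow, both in one group only.

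- **Absorbed benefit.** Any early fall in loneliness would lower the intervention baseline and disappear from the change score. The mixed model in section 3.7.1.1, with its group-by-time interaction, treats that baseline as the starting point and would not restore the loss.
- **Selection.** People who meet the Connector and disengage before the researchers call would not be enrolled, so the intervention cohort would lean towards early engagers.

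The study is non-randomised (section 3.3), so it depends more than a randomised trial would on comparable, pre-exposure baselines.

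**Working it through.** **Order of events as described**

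| Step | Who | Source |
|---|---|---|
| 1. Basic eligibility check, no scale named | Program manager | 3.4 |
| 2. Contact to arrange the meeting that starts the program | Connector | 3.4 |
| 3. Loneliness, isolation and depression screen, within element 1 | Connector | 3.4 |
| 4. Eligible people told of the evaluation | Connector | 3.5.1 |
| 5. Consent | Researchers | 3.5.1 |
| 6. Baseline, in the column after Screening and consent | Not stated for each scale | Table 3 |

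Section 3.4 is the only place that says who carries out the score-based screen and at what stage. Evaluation eligibility depends on that screen (3.5.1). If step 4 refers to people eligible on those scores, step 4 follows step 3, and by Table 3 step 6 follows both. That puts intervention-group baseline after element 1.

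The link that is not written down is between steps 4 and 6. Section 3.5.1 speaks of consent but not of baseline, and it does not date the Connector's invitation. The order is therefore inferred.

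**How a loss would scale**

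Inputs from section 3.6.2.3.1: fall in UCLA-3 of 0.85 points, effect size 0.37, alpha 0.05, power 0.9, 76 in the intervention group.

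The plan's own figure, from the one-sample (paired) normal formula, two-sided:

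n = ((1.960 + 1.282) / 0.37)² = 76.75, in line with the stated 76.

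Let f be the share of the effect already present at baseline. The article gives no value for f, so the values below are assumptions.

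- Remaining fall = 0.85 × (1 − f)
- Remaining standardised effect = 0.37 × (1 − f)
- Power on the plan's own basis = Φ(0.37 × (1 − f) × √76 − 1.960)

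| f | Remaining fall (points) | Standardised | Power, n = 76 |
|---|---|---|---|
| 0% | 0.85 | 0.37 | 0.90 |
| 10% | 0.77 | 0.33 | 0.83 |
| 20% | 0.68 | 0.30 | 0.73 |
| 30% | 0.60 | 0.26 | 0.62 |
| 50% | 0.43 | 0.19 | 0.36 |

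The one-sample basis is used only because it reproduces the plan's figure. The primary comparison is between groups, and whether 76 suits that comparison is a separate question. The selection effect cannot be sized from the article.

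**The case against.** The strongest reply is that the article permits a clean sequence. The manager checks eligibility before the Connector is involved, and section 3.4 uses the word eligible for that check, so the people invited in section 3.5.1 need not have completed element 1. The Connector's first act is only to arrange a meeting. The evaluation could be raised then, with consent and baseline completed by telephone before the program starts. Section 3.2 shows that a true before-and-after comparison is intended. The intervention rows of Table 3 and the service flow in Figure 3, which might settle the matter, were not legible in the text available and count neither for nor against.

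Much of this stands. A reader might infer that baseline UCLA-3, and hence every change score, definitely is taken after part of the intervention has been delivered. The article does not say so. A reader might also take Goal attainment at Baseline as proof, since goals do not exist until element 2. It is not: goals are recorded in the intervention group only, section 3.6.1 lets Connectors collect data while the program runs, and nothing says all baseline instruments are taken in one sitting. It shows that Baseline is used loosely in Table 3, no more.

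The mechanism is also open to challenge. The program aims to work by linking people to local activities, which happens in element 3, so one early conversation may not move UCLA-3 at all. And enrolling people who access the Connector is a declared feature of a pragmatic convenience sample (3.3), so selection is a lesser part of this point.

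What the reply does not supply is any statement that baseline comes first. The permitted clean sequence is possible but unstated, and it fits awkwardly with a score-based inclusion criterion whose only described screen is inside element 1. The order of consent, baseline and first exposure is something the article itself sets out, so it is fair to ask that it be set out unambiguously.

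**Conclusion.** The point holds as a gap in sequencing. The route described makes it likely that some or all intervention-group baselines follow the first Connector session, and no visible text prevents this. Comparators have no equivalent exposure. That sits badly with a change-from-baseline primary outcome and a before-and-after economic comparison.

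The expected bias, if the first session already helps, is attenuation. Its size cannot be derived from the article. It is zero if that session has no effect on UCLA-3; the 0.77 to 0.60 points left under an early share of 10–30% are illustrative, and nothing in the article anchors that range. Non-enrolment of people who disengage early is an additional effect of unknown size.

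The documents do not support saying that the baselines are known to be contaminated, or that a particular fraction of the effect is lost. Severity is moderate and confidence is moderate.

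**What to change.** Reconcile sections 3.2, 3.4, 3.5.1 and 3.6.1 (Table 3) as follows.

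1. Raise the evaluation at the program manager's existing first contact, and move the screening scales to that call.
2. State that consent and the baseline outcome scales are completed before the first face-to-face Connector meeting.
3. Label the first Goal attainment record as taken at goal-setting, not as a pre-intervention baseline.
4. Record the date of the first Connector meeting for every intervention participant.
5. For anyone whose baseline followed that meeting, report the number and repeat the primary analysis without them, as a sensitivity analysis.

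The cost is a short wait before the first Connector meeting and the transfer of the screening scales to an earlier call. No extra visit is needed. If practice already places baseline first, one sentence and a corrected Table 3 would resolve the timing.
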